##### Pre-specified stratification analysis based on size of effusion-synovitis (secondary analysis)

One hundred twenty-two participants at the end of the trial with Grade 2 or 3 effusion-synovitis will give us 80% power, and 5% probability of type 1 error (alpha=0.05) to detect a 12mm difference between diacerein and placebo on the VAS pain scale (SD of pain change 25.5 in the placebo group and 21.5 in drug group) in this participant sub-group. Based on the distribution of effusion-synovitis in our vitamin D trial for knee OA [55], we expect to recruit approximately 145 participants with either Grade 2 or 3 synovitis.

#### Effusion-synovitis (secondary outcome)

With 234 subjects, we will have over 99% power to detect a difference of 4.5ml, based on a SD of change of 7.44 in the placebo group and 6.74 in the drug group. These SDs have been estimated from our vitamin D trial for knee OA [8] using data from participants with Grade 1 or higher effusion-synovitis and a VAS score ≥ 40mm. We expect to see at least a reduction of 4.5 ml effusion-synovitis if diacerein effectively targets inflammation. While an MCID for effusion-synovitis is uncertain, a 4.5-ml reduction is approximately 2.5 times the change that could be expected with measurement error (±1.81mL [8]).

### Statistical analysis

The primary analyses will be intention-to-treat analyses of primary and secondary outcomes. Per protocol analyses will be performed as the secondary analyses, for study participants consuming ≥80% of study medication between baseline and week 24 (allowing for 1 capsule (50 mg) per day).

Changes in pain scores and total effusion volume will be analysed using a linear mixed-effects model with treatment, month and their interaction (treatment × month) as covariates. The correlation within trial centres and the repeated measures will be addressed using the trial centre and participant identification as random intercepts. Month will be treated as a random effect to allow different treatment effects among participants over time. Change in outcome measures within each group and difference of the changes between groups from baseline to follow-up will be calculated using linear combinations of the estimated coefficients adjusted for the baseline values of the corresponding outcome measure (e.g. change in pain scores will be adjusted for baseline pain scores). We will also run a model that additionally adjusts the primary outcome for sex, analgesic medication, and depression. Missing data caused by loss to follow-up and nonresponses will be addressed by adding baseline complete variables that can explain the missingness to the regression models.

Secondary analysis for missing data will be performed using multiple imputation by chained equations, with 20 imputations performed by the treatment group using baseline complete variables and nonmissing values of the outcomes at baseline and each follow-up, assuming missing at random.

The steering committee recommended that a doubling of serious adverse events (SAE) in one group compared to the other will trigger a safety review by the Data and Safety Monitoring Board (DSMB). If a safety review is triggered, the DSMB will review the unblinded data, and make recommendations about stopping the trial. A death (or other significant SAE) in the drug group may lead to stopping the study. When the DSMB reviews the unblinded data, they will make a judgement about whether the death/SAE is clearly attributable to the drug, and this will inform the decision about stopping the trial. No interim analyses will be conducted for efficacy. As this is a trial for OA (a non-life-threating condition), no level of efficacy would outweigh SAE concerns. An extraordinary meeting of the DSMB may be called by the Steering Committee at any time if there is concern about the number or severity of AEs.

Based on our hypothesis that diacerein will be more effective in participants with moderate to severe effusion-synovitis, we will perform a stratified analysis based on the size of effusion-synovitis at baseline (mL), and ordinal effusion-synovitis score (Grade 1 or 2/3) at baseline. Other pre-specified stratification analyses will be performed to examine which subgroups may respond better to treatment based on these variables: radiographic knee OA severity, degree of neuropathic pain, depression, fibromyalgia-ness, and co-pathology present on MRI. Statistical significance will be set as a two-sided *P* value <0.05.

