### Intervention

The treatment dose for this trial is diacerein 50 mg twice daily, as this is the recommended therapeutic dose for this drug. Eligible patients will start the trial taking one capsule daily with food, containing 50 mg of diacerein or identical placebo, for the first 2 weeks. This will then be increased to two capsules daily with food, equating to 100 mg of diacerein or identical placebo, to be taken for the remainder of the 24-week trial. The gradual increase in dose, as recommended by PRAC [24], aims to reduce the side effect of loose stool and diarrhoea caused by diacerein.

At 2 weeks, study staff will contact participants by telephone to assess any potential side effects and instruct them to increase dosage if appropriate. Depending on the side-effect profile participants report during the trial, it is possible for participants to remain on 50 mg/day after week 2 or for participants to reduce their dose from 100 mg/day back to 50 mg/day anytime during the trial. This decision will be made in consultation with the medical doctor at each site. The reason participants can remain on half the dose is that the effect of diacerein on pain improvement does not appear to be dose-responsive. For example, the literature suggests that 50 mg/day has a similar efficacy compared to 100 mg per day (− 15.6 vs − 18.3) [36].

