##### Adherence

At 12 and 24 weeks, participants will be asked to return all bottles (used or unused), such that adherence can be calculated based on pill counts [49]. All bottles (both returned and un-dispensed) are to be stored on site until the next Monitoring Visit. After reconciliation, returned bottles will be destroyed on-site.

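### The per-protocol rule is a single cumulative floor with an unassigned 1-capsule allowance, so it cannot separate sustained reduced-dose use from full-dose use that stops early

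*Protocol article*

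**What the plan says.** Intention-to-treat is the primary analysis. Per-protocol is a secondary analysis "for study participants consuming ≥80% of study medication between baseline and week 24 (allowing for 1 capsule (50 mg) per day" (Statistical analysis). Table 3 under Protocol amendments repeats this rule and explains that it follows from the change in permitted dose.

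Under Intervention, participants begin by "taking one capsule daily with food, containing 50 mg of diacerein or identical placebo, for the first 2 weeks". From week 3 until week 24 the schedule doubles, which is 100 mg a day in the active arm. Depending on side effects, "it is possible for participants to remain on 50 mg/day after week 2", and a later reduction is allowed after consulting the site doctor. The rationale given is that "the literature suggests that 50 mg/day has a similar efficacy compared to 100 mg per day (− 15.6 vs − 18.3").

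Under Adherence, bottles are returned at weeks 12 and 24 so that "adherence can be calculated based on pill counts [49"]. Table 1 shows capsules dispensed at weeks 0 and 12 and counted at weeks 12 and 24. Under Withdrawal, people who stop treatment are asked to complete the remaining assessments, and the drug's effect is said to last at least two months after stopping.

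**The concern.** A per-protocol set is meant to show the effect in people who took the treatment up to the time the outcome is measured, here week 24. This rule counts capsules over the whole 24 weeks and compares the total with a floor that allows one capsule a day. Most of the trial is scheduled at two a day, so a participant on the full schedule builds up the required total quickly. Nothing in the stated rule then requires any treatment in the second half.

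Such participants can have week-24 data, because those who stop treatment are asked to stay in follow-up. If they enter the set, the per-protocol estimate mixes people on treatment with people roughly three months off it. The wording also leaves open who receives the allowance, so two analysts could build different sets from the same data.

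**Working it through.** The plan gives the 80% threshold but no capsule count, so there is no printed figure to reproduce. The inputs come from Intervention (regimen and duration), Statistical analysis (threshold and allowance), and Table 1 and Adherence (dispensing and counts).

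**Capsules in the regimen**
- Duration: 24 × 7 = 168 days.
- Full schedule: 14 × 1 + 154 × 2 = 14 + 308 = 322 capsules.
- One capsule daily throughout: 168 capsules.

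**Reading A: the allowance applies to every participant**
- Floor: 0.80 × 168 = 134.4, so 135 whole capsules.
- Share of the full schedule: 135 / 322 = 42%.
- Full-schedule total by day 74: 14 + 2 × 60 = 134, which does not qualify.
- Full-schedule total by day 75: 14 + 2 × 61 = 136, which qualifies.
- Days left to week 24: 168 − 75 = 93, about 13 weeks.
- Someone who takes the scheduled capsules to week 12 and none afterwards has 14 + 70 × 2 = 154. That is 154 / 168 = 92% of the allowance, so this person also qualifies.

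**Reading B: the allowance applies only where a reduction was agreed**
- Full-dose floor: 0.80 × 322 = 257.6, so 258 capsules.
- Day reached: 14 + (257.6 − 14) / 2 = 135.8, or week 19.4.
- A participant who steps down part-way has no denominator in the text. For a reduction at week 12, for example, the prescribed total would be 154 + 84 = 238 and the 80% floor 0.80 × 238 = 190.4, or 191 capsules. The rule does not lead there.

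**What the count cannot distinguish**
- One capsule daily with 136 of 168 taken, spread over 24 weeks: 136 capsules.
- Full schedule to day 75, then nothing: 136 capsules.
- Under Reading A the rule treats these two participants identically.

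**Effect of splitting the count at week 12**
- Each period is 84 days. With the 1-capsule allowance, the floor is 0.80 × 84 = 67.2, or 68 capsules per period.
- Someone who takes nothing after week 12 scores 0 in the second period and is excluded.
- Someone at two a day reaches 68 in the second period after 34 days, on day 84 + 34 = 118, which is 50 days before week 24.
- With the prescribed full dose as denominator, the second-period floor is 0.80 × 168 = 134.4, or 135 capsules. At two a day it is reached during day 84 + 68 = 152, which is 16 days before week 24.

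**The case against.** The best defence is that the parenthesis was added because the amendment allowed reduction to 50 mg/day, so the allowance is naturally read as meant for participants on that dose. On that reading the week-11 stopping point disappears and the full-dose floor falls at about week 19.4. This is a fair account of the likely intention, but the rule itself does not say it, and it leaves mid-trial reductions without a denominator.

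A reader might infer that qualifying on 42% of the full schedule is itself a defect. The documents do not support that. The protocol permits 50 mg/day and gives a rationale, so a participant on that dose who takes 80% of it is following the protocol and belongs in the set.

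The stated carry-over also counts for the defence: someone who has stopped treatment is not necessarily uninformative. But the duration the protocol claims is at least two months, and the gap here is 93 days.

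Detailed adherence definitions can be left to an analysis plan. That would answer a missing detail, but here a rule is stated, and taken literally it admits people it should not.

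Finally, a stricter set conditions more heavily on behaviour after randomisation. That stands. Side effects drive dose reduction, and the protocol attributes loose stool and diarrhoea to the drug, so tightening the rule may increase selection on tolerability between arms.

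**Conclusion.** The concern holds as a fault in how the per-protocol set is defined. Depending on who receives the allowance, the floor for a full-dose participant is 135 or 258 capsules, and the earliest qualifying stop is day 75 or about week 19.4. The 93-day figure rests on Reading A and on capsules being taken as scheduled until stopping. It should not be presented as the only possible meaning of the text.

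Two stronger inferences are not supported. One is that the per-protocol result will be biased by a known amount or in a known direction between arms. Early stopping may plausibly be more common on active drug, but the documents give no rates. The other is that this is the only secondary analysis. The plan also has a multiple-imputation analysis and pre-specified stratified analyses.

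The consequence is confined to the secondary per-protocol analyses; the intention-to-treat primary analysis does not depend on the rule. It is worth correcting because the change is cheap and can be made before unblinding.

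**What to change.** Before unblinding, state in the analysis plan:

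1. The denominator is the number of capsules prescribed to that participant, counted at one per day beyond week 2 only for periods with an agreed reduction. The sponsor should confirm that dose level and dates of change are recorded, because the article does not say so.
2. The 80% threshold must be met separately in weeks 0–12 and weeks 12–24, using the existing week-12 and week-24 counts.
3. If dose level by period is not recorded, apply the existing 1-capsule allowance within each period, meaning at least 68 capsules in each. This is weaker, since a full-dose participant could still stop 50 days before week 24, but it excludes anyone who takes nothing after week 12.
4. The per-protocol result is supportive only, with a note that membership depends on tolerability.

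The cost is wording plus confirmation of what is recorded. No new visits or counts are needed and no permitted dose changes. The price is a smaller per-protocol set that selects more strongly on tolerability.

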### Study procedure and time points

Research assistants will first conduct telephone screening. Recruitment documentation will be posted to all individuals who satisfy telephone screening. Potential participants will have at least one week after receiving their recruitment documentation to read and consider a face-to-face visit or Telehealth screening. Patients will undergo, in sequential order, (i) clinical assessment with a medical doctor, as well as blood tests to ensure no contraindication to diacerein and a urine test in premenopausal women to rule out pregnancy, (ii) x-ray to confirm radiological disease and exclude severe knee OA, (iii) MRI of the study knee to determine presence of effusion-synovitis. If both knees are symptomatic and meet the ≥40mm/100 VAS inclusion criteria, then the knee with the worse pain and mild JSN will be studied.

For participants who are screened via Telehealth, the physical knee examination will be replaced by a verbal discussion with a medical doctor, talking through the ACR criteria. The study doctor will use the results of the verbal Telehealth knee exam, the participants’ medical history and medications, along with the participants’ x-ray and MRI scans to confirm the OA diagnosis and ensure it is safe for the participant to be enrolled in the study being guided by the current inclusion/exclusion criteria. During the Telehealth screening appointment, if something concerning comes up which requires face-to-face screening, the study doctor can either request the participant attend in person or exclude this participant if necessary.

Table 1 outlines the schedule of assessments. There will be 9 assessments (screening, weeks 0, 2, 4, 8, 12, 16, 20, and 24), and face-to-face clinic visits or Telehealth appointments will occur at screening, weeks 0, 12 and 24. The same research nurses, who are blinded to treatment allocation, will measure all clinical variables, administer questionnaires, monitor compliance, and record adverse events at these visits. Telephone contact and/or mail-outs (by email) will occur at the other time-points (weeks 2, 4, 8, 16, and 20). MRI scans will occur at screening and week 24; knee x-ray will be performed at screening.

**Table 1 Tab1:** Schedule of assessments

	Screening		Double-blind period							

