#### Secondary outcome measures

##### Improvement in effusion-synovitis at 24 weeks

A non-contrast MRI scan of the study knee will be performed at screening and week 24 using 1.5-T or 3-T whole-body MRI units with a commercial transmit-receive knee coil. For each participant, the study knee will be imaged in the sagittal plane using the same scanner at each study site. The following sequences will be used: (1) T2-weighted fat-saturated 3D fast spin echo sequence and (2) T1-weighted fat-saturated 3D gradient-recalled acquisition sequence (Table 2).

**Table 2 Tab2:** Magnetic resonance imaging sequences and parameters at the four study sites

	Machine and coils	T2-weighted sagittal 3D	T1-weighted sagittal 3D
Hobart	1.5 T whole-body MR unit (GE Optima 450W, Milwaukee, USA), using a dedicated Transmit/Receive 8-channel knee coil where patient size permits, if body habitus is too large, we use a 16-channel large GEM Flex coil	T2 weighted fat-saturated 3D fast spin echo sequence; flip angle 90°, repetition time 2300 ms; echo time 95 ms; field of view 18 cm; 256 × 256 matrix; 2 excitations; slice thickness 1 mm	T1-weighted fat-saturated 3D gradient recalled acquisition; flip angle 30°; repetition time 38 ms; echo time 3 ms; field of view 16 cm; 256 × 256 matrix; 1 excitation; slice thickness 1.5 mm
Melbourne	3 T whole-body MR unit (Siemens, Magnetom Avanto Fit, Erlangen, Germany), using a dedicated Transmit/Receive 15 channel knee coil	T2 weighted fat-saturated 3D fast spin echo sequence; flip angle 120°; repetition time 1200 ms; echo time 50 ms; field of view 16 cm; 256 × 320 matrix; 1 excitation; slice thickness 0.6 mm	T1-weighted fat-saturated 3D gradient recalled acquisition; flip angle 30°; repetition time 11.7 ms; echo time 5.61 ms; field of view 16 cm; 320 × 320 matrix; 1 excitation; slice thickness 1.5 mm
Perth	1.5 T whole-body MR unit (Siemens, Magnetom Avanto Fit, Erlangen, Germany), using a dedicated Transmit/Receive 15 channel knee coil	T2 weighted fat-saturated 3D fast spin echo sequence; flip angle 90°; repetition time 2302 ms; echo time 81 ms; field of view 18 cm; 256 × 256 matrix; 2 excitations; slice thickness 1 mm	T1-weighted fat-saturated 3D gradient recalled acquisition; flip angle 30°; repetition time 17.7 ms; echo time 3.5 ms; field of view 18 cm; 256 × 160 matrix; 1 excitation; slice thickness 1.4 mm

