Adelaide	3 T whole-body MR unit (Siemens, Magnetom Skyra 3Tesla), using a dedicated 15-channel knee coil	T2 weighted fat-saturated 3D SPACE; flip angle 120°; repetition time 2200 ms; echo time 121 ms; field of view 16 cm; 320 × 259 matrix; 1 excitation; slice thickness 0.6 mm	T1-weighted Water Excitation 3D gradient recalled acquisition VIBE; flip angle 16°; repetition time 10.4 ms; echo time 5.7 ms; field of view 160 cm; 320 × 320 matrix; 1 excitation; slice thickness 1 mm

Effusion-synovitis volume (mL) will be distinguished in the following subregions according to the anatomy of the knee joint synovial cavity [37]: (1) the suprapatellar pouch, extending superiorly from the upper surface of the patellar, between the posterior suprapatellar fat pad (quadriceps femoris tendon) and the anterior surface of the femur; (2) other cavity, which includes the area between the central femoral and tibial condyles, around the ligaments and menisci, and the area behind the posterior portion of each femoral condyle, inside of the joint capsule. The volumes of individual joint subregions will be isolated from the total volume by selecting each region of interest (ROI) according to the intra-articular fluid-equivalent signal on a section-by-section basis. The final 3-dimensional volume rendering will be generated using commercial in-house imaging software. The readers will be blinded to treatment allocation and participant information. Intra- and inter-observer repeatability for this measurement method is excellent, with an intraclass correlation coefficient (ICC) of 0.95–0.98 and 0.93–0.99, respectively [8]. Change in total effusion-synovitis volume and volume at each sub-region will be calculated as follow-up volume minus baseline volume.

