### Withdrawal

If participants withdraw from the study before 24 weeks of follow-up, the reason and date will be recorded in the Withdrawal Form. Diacerein remains effective for at least two months after treatment is stopped [20]; therefore, to minimise missing data in this study, participants that withdraw from treatment will be asked if they are willing to complete any or all of the remaining assessment items, and any consent given will also be noted in the Withdrawal Form. Participants who choose to withdraw from the trial will be asked permission for the continued use of their blood samples (and data). These participants will be invited to do a second MRI scan as soon as possible, and to complete clinic visits and surveys as they come due until 24 weeks.

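### Effusion volume has at most two scans per participant but is given the longitudinal model built for pain; random month is not identified and the promised baseline adjustment is not delivered

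*Protocol article*

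**What the plan says.** The Statistical analysis section of the protocol article puts pain and effusion volume under one model: "Changes in pain scores and total effusion volume will be analysed using a linear mixed-effects model with treatment, month and their interaction". It handles clustering and repeated measures "using the trial centre and participant identification as random intercepts", and adds: "Month will be treated as a random effect to allow different treatment effects among participants over time". Within-group changes and between-group differences in change are to come from linear combinations of the coefficients, "adjusted for the baseline values of the corresponding outcome measure". No exception is made for effusion volume.

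The imaging schedule is much thinner than the pain schedule. Under Study procedure and time points: "MRI scans will occur at screening and week 24; knee x-ray will be performed at screening". The schedule of assessments (Table 1) and the outcome section agree: "A non-contrast MRI scan of the study knee will be performed at screening and week 24". The outcome is then reduced to one number: "Change in total effusion-synovitis volume and volume at each sub-region will be calculated as follow-up volume minus baseline volume". For people who withdraw, the Withdrawal section says: "These participants will be invited to do a second MRI scan as soon as possible". That can move the second scan earlier but does not add a third. Pain on the VAS is collected at baseline and at weeks 4, 8, 12, 16, 20 and 24.

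**The concern.** A model with a participant intercept, a participant-specific month effect and residual error needs enough repeated measurements to tell these apart. Pain has them and effusion volume does not. A decrease in effusion-synovitis is one of the stated secondary hypotheses and has its own power statement, so its analysis should be runnable as written.

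Two things are at stake. First, the analyst would have to drop or restrict terms after seeing the model fail or return arbitrary variance components, and the plan does not say which. Second, the simplification most likely to be adopted (both scans as rows, participant intercept, baseline volume as covariate) does not give the baseline-adjusted comparison of change that the plan promises.

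**Working it through.** **1. The plan's own figure.** Inputs from Sample size calculations, Effusion-synovitis: 234 participants (117 per arm under 1:1 allocation), difference 4.5 mL, SD of change 7.44 (placebo) and 6.74 (drug), two-sided alpha 0.05.

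- Pooled SD = sqrt((7.44² + 6.74²)/2) = 7.10
- SE = 7.10 x sqrt(2/117) = 0.928
- 4.5/0.928 = 4.85; power = Φ(4.85 − 1.96) = 0.998

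The claim of more than 99% reproduces. It is a two-sample comparison of one change per participant.

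**2. Change as response.** With every second scan at month 6, the fixed-effect rows (intercept, treatment, month, treatment x month) are (1, 0, 6, 0) and (1, 1, 6, 6). The rank is 2 of 4, so month is aliased with the intercept and treatment x month with treatment. One row per participant gives one variance element for 3 or 4 variance parameters, so neither participant intercept nor random month separates from the residual.

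**3. Both scans as response rows.** The fixed-effect rank is 4 of 4 and a participant intercept is estimable. The two scans supply 3 distinct covariance elements: two variances and one covariance. Intercept variance, month variance, their covariance and the residual make 4 parameters, and the mapping has rank 3. With month scaled 0/1 and assumed variances 60 and 60 with covariance 35, these splits all give the same matrix:

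| Intercept var | Month var | Covariance | Residual |
|---|---|---|---|
| 35 | 0 | 0 | 25 |
| 50 | 30 | −15 | 10 |
| 45 | 20 | −10 | 15 |

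If the intercept-month covariance is set to zero, which the plan does not state, there are 3 parameters for 3 elements. The month variance is then the week-24 variance minus the screening variance. In simulations with 234 participants it fell at zero in 47% of data sets with equal variances, and in more than 99% when the week-24 variance was lower (45 against 60, assumed).

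**4. Contrast with pain.** Seven assessments give 28 covariance elements for the same 4 parameters (rank 4), so the model is identified there.

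**5. Baseline adjustment with both scans as rows.** Baseline volume takes the same value on both of a participant's rows, so with complete data it cannot alter the within-participant contrast. The treatment x month estimate stays equal to the raw difference in mean change; simulated fits agreed to about 1e-13.

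The standard error does move. Assume equal variances (scaled to 1) and correlation ρ:

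- The shared baseline coefficient is (1 + ρ)/2.
- The two residuals then have covariance −((1 − ρ)/2)². This is negative, so the participant-intercept variance goes to zero.
- The pooled residual variance is (1 − ρ)(3 + ρ)/4. The model's variance for a change is twice that, against a true 2(1 − ρ).
- SE ratio = sqrt((3 + ρ)/4).

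| Assumed ρ | Baseline coefficient | Model SE / correct SE | Implied type I error | ANCOVA SE below change-score SE |
|---|---|---|---|---|
| 0.3 | 0.65 | 0.908 | 7.5% | 19% |
| 0.6 | 0.80 | 0.949 | 6.3% | 11% |
| 0.8 | 0.90 | 0.975 | 5.6% | 5% |

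The last column is 1 − sqrt((1 + ρ)/2). Simulated fits with 117 per arm gave mean SE ratios of 0.91, 0.95 and 0.97.

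**The case against.** **The treatment effect survives.** The plan's linear combinations suit having both scans as rows, and there the fixed effects are estimable. In simulated data the model with a redundant random month still returned the difference in mean change with the right standard error (−5.102, SE 0.957, as in the random-intercept model and the plain comparison). This stands. A reader might infer that nothing in the model can be estimated for effusion; that is true only of the change-score form at a common scan time. With both scans as rows, only random month fails.

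**The parameter count needs an intercept-month covariance that the plan does not mention, and an SAP might fix the structure.** Setting that covariance to zero does make the model just identified. But the article names the outcome and states the model, and the restriction is not in the text.

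**Early scans break the aliasing.** If actual scan month is used and some withdrawn participants in each arm are scanned early, the change-score fixed-effect design reaches rank 4. That is correct, but the month terms would then rest entirely on people who stopped, which is no basis for the main contrast.

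**Baseline does some work.** A reader might infer that the baseline row is predicted perfectly. It is not: the shared coefficient is about 0.65 to 0.90 at the assumed correlations, not 1. The contrast at week 24 also moves with adjustment (in one simulated data set from −4.31 to −3.63, against −3.75 from ANCOVA). But the plan asks for the difference in changes, and that estimate does not move.

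**Power is not threatened.** This stands. The calculation already uses an unadjusted SD of change.

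**Conclusion.** The point holds as a moderate issue for a secondary outcome. The stated model does not fit a two-scan endpoint: with change as response most of its terms are aliased, and with both scans as rows random month is unidentified without an unstated restriction. In the second form the promised baseline adjustment leaves the treatment x month estimate unchanged and makes its standard error about 2.5% to 9% too small.

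The aliasing and rank results follow from the schedule, given a common week-24 scan time. The standard-error figures assume complete data, equal variances at the two scans and correlations of 0.3 to 0.8. The documents give neither a correlation nor the SD of volume at each scan.

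The documents do not support reading this as a threat to the primary analysis, to the effusion power statement or to the validity of the unadjusted treatment estimate.

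**What to change.** In the Statistical analysis section, take total effusion volume out of the sentence it shares with pain and give it its own model: ANCOVA of week-24 volume (or change) on treatment, baseline volume and site, one row per participant, reporting the treatment coefficient with its 95% CI. The effusion-synovitis grade used to stratify randomisation may be added as a covariate. State how a second scan taken early after withdrawal enters this analysis. Keep the repeated-measures model with random month for pain.

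The cost is a wording change to the analysis text and a simpler analysis. No data collection, sample size or power statement changes. The expected gain over an unadjusted change score is a standard error about 5% to 19% lower, for assumed correlations from 0.8 down to 0.3.
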